**AIM**:

To determine whether high-amylose maize starch (HAMS) in hypo-osmolar (reduced osmolarity) ORS will reduce stool output and lessen duration of diarrhoea in patients with cholera or cholera-like illness, when compared to glucose-containing hypo-osmolar (reduced osmolarity) ORS.

**SUBJECTS**:

Inclusion Criteria:

1. Males aged between 12 years to 65 years.
2. Profuse watery diarrhoea of 3 days duration or less.
3. Moderate to severe dehydration at presentation.

Exclusion Criteria:

1. Bloody diarrhoea.
2. Concurrent major medical illness including cardiac, renal or liver disease or internal malignancy.

**STUDY PROTOCOL**:

1. Patients will be recruited from the Emergency Services (Casualty) of the Christian Medical College & Hospital, Vellore.
2. The Casualty Medical Officer (CMO) will page the study medical research officer when male patients with acute watery diarrhoea and moderate to severe dehydration present to Emergency Services.
3. The CMO will resuscitate the patient, placing a wide bore peripheral or central venous line as per clinical judgement, and running in intravenous Hartmann’s Ringer lactate at a total dose of 100 ml/kg as per WHO treatment guidelines.
4. Blood samples will be collected for blood counts, urea, creatinine and electrolytes.
5. The nurse will send stool samples for culture (*Vibrio cholerae* and enteric bacterial pathogens) as soon as feasible.
6. A single oral dose of Doxycyline 300 mg will be given.
7. The study medical officer will evaluate the patient for eligibility and obtain informed written consent from patient or relative if eligible.
8. The study medical officer will re-evaluate the patient four hours after commencing intravenous rehydration in order to confirm that the patient can enter the trial.
9. Eligible patients who have been consented will be transferred to the gastroenterology metabolic ward for further treatment.
10. On reaching the ward, the study medical officer and nurses will evaluate the patient and again explain the details of the study including the need to take oral rehydration solution, the manner in which it is to be taken, and details regarding food intake, stool collection and urine collection.
11. Each patient that enters the ward and is ready to receive ORS will be given a packet labeled with the next serial study number and containing 50 sachets of ORS (for reconstitution to 200 ml each).
12. Serial study numbers will be randomly allocated to one of the two ORSs being studied using a table of random numbers, and the code retained with the study co-ordinator in a sealed envelope. Sachets of the two ORSs will be packaged accordingly. Backup packets with additional ORS sachets will be available for each study number.
13. Patients will be provided a plastic measuring cylinder for making up the ORS. They will be advised to use bottled water for making up the ORS. They will be instructed to take 200 ml ORS per hour and 200 ml after each loose stool. The ORS will be mixed and administered by the study nurse or by the patient’s attendant.
14. Patients will be provided bottles for urine collection, and buckets lined with plastic bags for stool collection. A chart for recording time of each stool, as well as the consistency of each stool will be given to each patient and the attendant of the patient will be instructed to complete this.
15. A normal south Indian diet will be provided to the patient and he will be encouraged to take this while ORS administration is continuing.
16. One study nurse will be constantly available, by rotation, to ensure that the patient receives ORS and collects stool and urine quantitatively.
17. The study medical officer will review the patient every four hours or more frequently in the first day, in order to ensure that hydration is maintained and renal function is not compromised.
18. As it is difficult to mask the starch containing ORS, the study medical officer should avoid asking about the kind of ORS which the patient is receiving.
19. Stool collected in individual labeled plastic bags will be taken to the faecal laboratory by the ward attender and left in a designated place. These bags will be weighed periodically by the paramedical worker assigned to the study team, who will record the weight and consistency and then send the bags for incineration. This paramedical worker will not come into contact with the patient or study nurses and will have no knowledge of the intervention received or the actual intent of the study.
20. Urine output will be recorded with time of voiding.
21. Serum creatinine and electrolytes will be measured after 6-12 hours in patients whose urine output or renal function is not satisfactory, and after 24 hours in all patients.
22. In any patient whose dehydration is not adequately corrected (as evidenced by clinical signs of dehydration including a persistently low urine output) or who continues to have profuse diarrhoea exceeding 10 ml/kg/hour, intravenous fluids may be administered according to the clinical judgement of the medical officer supervising the study. All fluid intake is to be recorded including such unscheduled intravenous fluid administration.
23. Patients will be discharged after 48 hours or when their diarrhoea has ceased, whichever occurs later.
24. In an individual patient, the study will end at the point when the first formed stool is observed. This time must be noted for each patient.
25. The major or primary **end-points** of the study are:
26. Stool weight in the first and second 12 hour periods
27. Stool weight in the second 24 hours
28. Time from first ORS administration to first formed stool

26. Other or secondary end-points include:

1. Amount of ORS consumed during 0-24 and 24-48 hours
2. Incidence of unscheduled IV treatment in the two study arms
3. Incidence of complications – hypokalaemia (serum potassium <3.5 mE/L), hyponatraemia (serum sodium <130 mE/L).

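### The protocol does not say whose consistency reading defines the primary time to first formed stool, so a probably unmasked bedside call can set it although a masked reading is also collected.

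*Protocol*

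**What the plan says.** All references are to the Protocol, section STUDY PROTOCOL.

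- **End-point.** The primary list includes "Time from first ORS administration to first formed stool".
- **Event rule.** Under item 24, for each patient "the study will end at the point when the first formed stool is observed", and "This time must be noted for each patient". No observer, source record or criterion for formed is given.
- **Bedside record.** Item 14 provides "A chart for recording time of each stool, as well as the consistency of each stool", and "the attendant of the patient will be instructed to complete this".
- **Who handles the ORS.** Item 13 says "The ORS will be mixed and administered by the study nurse" and names the patient's attendant as the alternative.
- **Masking.** Item 18 opens "As it is difficult to mask the starch containing ORS"; the safeguard it then gives is that the medical officer should not ask which ORS the patient is taking.
- **Laboratory record.** Item 19 sends stool in separately labelled bags to a paramedical worker "who will record the weight and consistency and then send the bags for incineration". That worker is kept away from patients and nurses and is unaware of the allocation and of the purpose of the study.

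**The concern.** Whether a stool is formed or still loose is a judgement, and the protocol gives no criterion for it. When such a judgement fixes a primary end-point, it should be made by someone who does not know the arm. The protocol sets up such a reader in item 19, but never says that this reading decides the event. The event rule in item 24 instead reads most naturally as a call made as the stool is passed. The people then present are the attendant and the nurse, and either may have prepared an ORS that the protocol itself regards as hard to disguise.

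If bedside readers tend to call stools formed sooner in one arm than in the other, the difference passes straight into the comparison of durations. The stool-weight end-points are better protected, because the masked worker does the weighing.

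**Working it through.** No sample-size or power figure bears on this point, so the check is a tracing of who records what.

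**1. What the end-point needs.** It needs an event (a consistency judgement) and a clock time for that event.

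**2. Which record supplies each.**

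| | Bedside chart (item 14) | Laboratory record (item 19) |
|---|---|---|
| Kept by | Patient's attendant | Paramedical worker |
| Likely to know the arm | Possibly: may mix the ORS (item 13), which is hard to mask (item 18) | No |
| Consistency | Yes, each stool | Yes, from separately labelled bags |
| Time of passing the stool | Yes | Not mentioned; bags are weighed periodically |
| Stated role in the end-point | None stated | None stated |

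Neither record is named as the source. The masked record has the better judgement but no stated time. The bedside record has the time, but its judgement is exposed.

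**3. Who could be the observer in item 24.**

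- *Attendant:* reads each stool and writes down its time; may prepare the ORS.
- *Study nurse:* always available to see that stool is collected (item 16); also may prepare the ORS (item 13).
- *Medical officer:* reviews every four hours or more often on the first day (item 17); is told not to ask about the ORS, but is not assigned to read stools.
- *Laboratory worker:* masked, but sees bags some time after they are filled, so cannot end a patient's study at the moment of the event.

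Item 24 excludes none of the four. An end of study at the moment of observation fits the first two best.

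**4. Use of the masked consistency reading.** The other primary end-points are stool weights. The secondary ones are ORS intake, unscheduled intravenous treatment and electrolyte complications. None uses consistency, so the only end-point that the masked reading could serve is this one.

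**5. Size.** For one patient, let the error be the recorded time minus the time at which the stated criterion was first met. Then

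bias in the mean difference = mean error in the HAMS arm − mean error in the glucose arm.

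Misreading that is equal in both arms cancels; only the difference counts. A premature call contributes an error equal to minus the interval to the first stool that truly qualifies. The document gives no stool frequency late in the illness, no rate of misreading, no expected duration and no target difference. Neither term can be filled in, and there is no planned effect to compare the result with.

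**6. What can be repaired later.** A statistical analysis plan could name the source record. It could not add a time to a bag that was labelled without one and then incinerated, nor recover stools that were not bagged after a bedside call.

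**The case against.** The strongest reply is that item 24 is in the passive and does not give the decision to the attendant. A formed stool can also be observed in the laboratory. Since no other listed end-point uses consistency, the masked reading may well have been meant for this one, with the time taken from the chart. Which of two collected records feeds an end-point is also commonly left to the analysis plan, which is not shown. This stands as far as it goes: the protocol leaves the matter open and has not demonstrably chosen the unmasked reading. It does not remove the need for labels and a collection rule that make the masked reading usable.

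Four stronger readings are tempting and are not supported:

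- *That the end-point rests on the attendant's reading, or can only be called at the bedside.* This is an inference from the timed chart and the wording of item 24. The document does not say it.
- *That the attendant knows the arm.* Packets carry a study number and the code is sealed (items 11 and 12). Item 18 says that masking is difficult, not that it fails, and the attendant only may mix the ORS. Probably unmasked is as far as the text goes.
- *That a bedside call stops stool collection and so truncates the stool weight of the second 24 hours.* Item 24 ends the study but is silent on collection, and item 23 keeps patients for at least 48 hours. Whether bagging continues is unclear.
- *That the masked worker reads every stool.* Separate bags suggest it, but it is not stated.

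**Conclusion.** The point holds as a gap in how a primary end-point is ascertained. The protocol collects one masked and one probably unmasked consistency reading, does not say which defines the first formed stool, and attaches a time only to the second. A bedside judgement by an attendant or nurse can therefore set the end-point.

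This rests on two assumptions: that some attendants or nurses can tell the two solutions apart, which item 18 makes likely, and that borderline stools occur, which the absence of a criterion makes harder to handle. No figure in hours is defensible from this document, and neither arm can be said to be favoured. The change is worth making because it is cheap, and because part of the defect cannot be mended once the bags have been destroyed.

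**What to change.** Amend items 14, 19 and 24 together:

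1. Define *formed* by one stated criterion, used by both readers.
2. Define the first formed stool as the first one meeting that criterion in the laboratory worker's record. Take its time from the bedside chart.
3. Put the study number and the time of passing the stool on each bag label, with nothing that identifies the ORS.
4. Go on bagging and labelling stools after a bedside call of formed for as long as the patient remains on the ward under item 23, so that a premature call can be corrected.
5. State that the masked reading prevails if the two records disagree. Keep the attendant's consistency column for ward use.

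The worker and the bags are already in place, so no staff are added. There are a few more bags to read, and the event time is assigned after the fact rather than at the bedside. One limit remains: if a patient leaves soon after a bedside call that the masked reading does not confirm, no later stool is available. The protocol should say that such a patient is censored at the last bagged stool.

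### Secondary end-point 3 (low potassium or sodium) does not say which samples count, while item 21 adds an early test only for patients doing badly, so detection may differ between arms

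*Protocol*

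**What the plan says.** All references are to the Protocol, section STUDY PROTOCOL.

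- **End-point.** The third secondary end-point is "Incidence of complications – hypokalaemia (serum potassium <3.5 mE/L), hyponatraemia (serum sodium <130 mE/L". Nothing more is given: no sampling time, no period, no baseline rule. By contrast, the first secondary end-point (ORS consumed) does state its windows, 0-24 and 24-48 hours.
- **Sampling on treatment (item 21).** The early test is conditional and carries no numeric trigger: "Serum creatinine and electrolytes will be measured after 6-12 hours in patients whose urine output or renal function is not satisfactory". The later test in the same item is universal; every patient in both arms has it at 24 hours.
- **Sampling at presentation (item 4).** "Blood samples will be collected for blood counts, urea, creatinine and electrolytes". This is listed under care in Emergency Services, ahead of allocation on the ward (items 11 and 12): "Each patient that enters the ward and is ready to receive ORS will be given a packet labeled with the next serial study number".
- **Masking (item 18).** "As it is difficult to mask the starch containing ORS, the study medical officer should avoid asking about the kind of ORS". Item 17 has the same officer review hydration and renal function at least four-hourly on the first day.
- **Rescue fluid (item 22).** Where dehydration persists, with low urine output as one of its signs, or diarrhoea stays profuse, "intravenous fluids may be administered according to the clinical judgement of the medical officer supervising the study".
- **Eligibility.** The section SUBJECTS lists no exclusion for low potassium or sodium at presentation.

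**The concern.** A threshold incidence depends on how often a patient is tested. Here everyone has one on-treatment test, and some have a second chance to fall below the cut-off. Who gets it depends on urine output and renal function after ORS has begun. Those reflect hydration, which the trial expects the ORS to change. If one arm stays better hydrated, the other is tested more and can show more low values even when its electrolytes are no worse. The aim is that starch ORS lessens diarrhoea. If that is right, the extra testing would fall mainly on the glucose arm and make the starch ORS look safer than it is; the direction is not known in advance.

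A second, separate matter is the patient who arrives low and is still low at 24 hours. The end-point does not say whether he counts as a complication of his allocated ORS. At stake is how far the electrolyte safety comparison can be read. The stool-weight and time-to-formed-stool end-points do not depend on it.

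**Working it through.** The protocol gives no event rate, sample size, power or significance level, so there is no stated figure to reproduce. The inputs taken from it are the sampling schedule (items 4 and 21), the cut-offs (secondary end-point 3) and the order of sampling and allocation (items 4, 11 and 12). **Every rate below is an assumption**, used only to show size.

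**Step 1. Unequal early testing, equal true risk.** Let p be the chance of a low value at 24 hours, q the chance of being low at 6-12 hours but normal at 24 hours (among those tested early), and f the share of an arm tested early. If any low on-treatment value counts:

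observed incidence = p + f × q, so the difference between arms = (f_A − f_B) × q.

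p cancels. With p anywhere from 10% to 30%:

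| Early-test shares | q = 5% | q = 10% | q = 20% |
|---|---|---|---|
| 20% v 20% | 0 | 0 | 0 |
| 30% v 10% | 1 point | 2 points | 4 points |
| 50% v 10% | 2 points | 4 points | 8 points |

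Example at p = 20%, q = 20%, shares 50% v 10%: 0.20 + 0.5 × 0.20 = 0.30, against 0.20 + 0.1 × 0.20 = 0.22.

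**Step 2. Another way to set q.** Give each test the same chance p of a low result.

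- Independent tests, q = p(1 − p). At p = 0.2, q = 0.16; shares 20% v 40% give 0.2 + 0.2 × 0.16 = 23.2% and 0.2 + 0.4 × 0.16 = 26.4%, a gap of 3.2 points. At p = 0.3, q = 0.21; shares 10% v 40% give 0.3 + 0.1 × 0.21 = 32.1% and 0.3 + 0.4 × 0.21 = 38.4%, a gap of 6.3 points.
- Tests in one patient hours apart are unlikely to be independent. With a bivariate normal correlation of 0.5, the chance of at least one low value in two tests is 0.313 (p = 0.2) or 0.443 (p = 0.3), so q = 0.113 or 0.143. The gaps become 0.2 × 0.113 = 2.3 points and 0.3 × 0.143 = 4.3 points.

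These all lie inside the 1 to 8 points of Step 1.

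**Step 3. The 24-hour sample alone.** Observed incidence = p in each arm. f drops out, and arms with equal true risk show a difference of 0 whatever the early-testing pattern.

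**Step 4. Patients already low at presentation.** Let b be the share low at presentation, the same in both arms in expectation because the sample precedes allocation. Assume new-onset risks of 20% v 10% among the rest, and suppose every patient low at presentation counts:

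observed incidence = b + (1 − b) × new-onset risk, so the difference = (1 − b) × 10 points.

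| b | Observed | Difference | Risk ratio | n per arm |
|---|---|---|---|---|
| 0% | 20% v 10% | 10 points | 0.50 | 199 |
| 10% | 28% v 19% | 9 points | 0.68 | 348 |
| 20% | 36% v 28% | 8 points | 0.78 | 533 |
| 30% | 44% v 37% | 7 points | 0.84 | 771 |
| 40% | 52% v 46% | 6 points | 0.88 | 1089 |

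The last column is the usual two-proportion size for two-sided 5% and 80% power. With equal new-onset risks the difference is 0 at every b: this is dilution, not a false difference.

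**The case against.** The strongest reply is that nothing in the protocol is stated wrongly. Item 21 is a monitoring schedule; no sentence puts the 6-12 hour result into the end-point, and the same item supplies a 24-hour sample for everyone. Which sample enters a secondary safety summary, and how baseline is handled, is commonly left to a statistical analysis plan, and one may exist. This stands in part: equal detection is obtainable from the data already planned. But the protocol itself fixes both a selective schedule and a bare threshold, and no later plan can create early samples that were never taken.

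Two stronger readings are tempting, and the text supports neither.

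- A reader might infer that the end-point does count values low at presentation, or does mix early and 24-hour results. The protocol is silent on both, and incidence can be read as new onset.
- A reader might infer that low presentation values add to the unequal detection. They precede allocation and are balanced in expectation, so they dilute only.

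It is also fair that the link to an unmasked officer is inferred. Item 21 does not say who judges the trigger; the link comes from items 17 and 18. Urine output is recorded with times (item 20), so the trigger rests partly on recorded data.

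Finally, a 24-hour-only comparison has a weakness. Low urine output can prompt both the early test and unscheduled intravenous fluid, so some 24-hour values may follow that treatment and could hide earlier low ones. A new-onset count alone would also miss a patient who arrives mildly low and falls much further. Both points stand and shape the fix.

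**Conclusion.** The point holds as a conditional one. End-point 3 leaves open which samples count, and item 21 tests early only in patients doing badly after ORS has started. A false difference needs two things together: early values must count, and early-test shares must differ between arms. Given both, the excess in the more-tested arm is about 1 to 8 points for q of 5% to 20% and shares of 30% v 10% or 50% v 10%. It is zero at equal shares. Counting patients already low at presentation would shrink an assumed 10-point contrast to 6 to 9 points for b of 10% to 40%, without creating one. None of these rates comes from the protocol. Severity is minor to moderate: this is a secondary safety end-point, and the primary end-points are untouched.

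**What to change.** Reword secondary end-point 3 so that:

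1. the between-arm comparison uses the 24-hour sample that item 21 requires in all patients;
2. 24-hour potassium and sodium are compared as continuous values, adjusted for the presentation value from item 4, so that a further fall in someone already low is not lost;
3. incidence below each cut-off at 24 hours is reported, with new-onset cases shown separately from patients already low at presentation;
4. the 6-12 hour values are reported by arm as safety data, with the number tested in each arm, alongside unscheduled intravenous fluid use, because 24-hour values in those patients may follow that treatment.

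The cost is a change of wording. The samples are already scheduled, and neither testing nor care changes. The price is that low values seen only at 6-12 hours leave the formal comparison; item 4 of this list keeps them in view.
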